## Abstract

**Introduction:**

Transparent and accurate reporting is essential for readers to adequately interpret the results of a study. Journals can play a vital role in improving the reporting of published randomised controlled trials (RCTs). We describe an RCT to evaluate our hypothesis that asking peer reviewers to check whether the most important and poorly reported CONsolidated Standards of Reporting Trials (CONSORT) items are adequately reported will result in higher adherence to CONSORT guidelines in published RCTs.

**Methods and analysis:**

Manuscripts presenting the primary results of RCTs submitted to participating journals will be randomised to either the intervention group (peer reviewers will receive a reminder and short explanation of the 10 most important and poorly reported CONSORT items; they will be asked to check if these items are reported in the submitted manuscript) or a control group (usual journal practice). The primary outcome will be the mean proportion of the 10 items that are adequately reported in the published articles. Peer reviewers and manuscript authors will not be informed of the study hypothesis, design or intervention. Outcomes will be assessed in duplicate from published articles by two data extractors (at least one blinded to the intervention). We will enrol eligible manuscripts until a minimum of 83 articles per group (166 in total) are published.

**Ethics and dissemination:**

This pragmatic RCT was approved by the Medical Sciences Interdivisional Research Ethics Committee of the University of Oxford (R62779/RE001). If this intervention is effective, it could be implemented by all medical journals without requiring large additional resources at journal level. Findings will be disseminated through presentations in relevant conferences and peer-reviewed publications. This trial is registered on the Open Science Framework (https://osf.io/c4hn8).

Strengths and limitations of this studyPragmatic randomised controlled trial (RCT) with individual randomisation of real manuscripts describing RCTs submitted to a variety of journals.Main outcomes will be assessed from publicly available sources (ie, published articles).If this simple intervention is effective, it could be implemented by journals without requiring large additional resources at journal level.The intervention could not be included within the email from journal with the link to the manuscript for review, risking peer reviewers will potentially ignore the separate email containing the CONsolidated Standards of Reporting Trials reminder.

## Introduction

### Background and rationale

There is substantial agreement that well conducted and reported randomised controlled trials (RCTs) generate the most trustworthy evidence when evaluating newly developed or existing clinical interventions.^1–3^ For clinicians, scientists and decision makers, published articles are often the only way to know how a study was conducted. In order to judge the internal and external validity of RCTs, it is crucial that these articles present transparent, accurate and unbiased information about the methods and conduct of the RCT.

To improve the quality and transparency of clinical and epidemiological research, the EQUATOR (Enhancing the Quality and Transparency of Research) Network was founded in 2006 and officially launched in 2008.^4–10^ This international network, which assists in the development of reporting guidelines and actively promotes their use, consists of methodologists, epidemiologists, reporting guideline developers, statisticians, clinicians and journal editors.

The CONsolidated Standards of Reporting Trials (CONSORT) is perhaps the most prominent reporting guideline, designed to help improve the transparency and quality of reporting of RCTs.^11–13^ It guides authors, peer reviewers and journal editors on the minimum information to be included in published reports of RCTs to facilitate critical judgement and interpretation of results and consists of 25 items and a flow diagram. The last update of the CONSORT Statement was published simultaneously in 10 leading medical journals in 2010^13^ and currently CONSORT is endorsed by over 600 journals worldwide.^14^

Despite some improvement in reporting following the endorsement of the CONSORT statement, there remain major reporting deficiencies in published RCTs.^3 15–21^ For example, a study of 1122 RCTs indexed in PubMed in December 2012 found that many did not define the primary outcome (31%), state the sample size calculation (45%) or explain the method of allocation concealment (50%).^22^ This lack of transparency is a major limiting factor for readers who assess an article in order to find the answer to a specific question; it is also a major problem for scientists who perform systematic reviews and meta-analyses.

### Evidence to date

Journals can play a vital role in improving the reporting of published RCTs. For example, a survey of journals’ ‘Instructions to Authors’ in 2014 found that 63% (106 of 168) of biomedical journals mentioned CONSORT^23^; however of those journals only 38 (36%) required a completed CONSORT checklist on submission. Such implementation indicates some improvement over time compared with an assessment in 2007 when only 17 of 62 (27%) journals requested the CONSORT checklist on submission.^24^ A study using interrupted time series analysis and assessing if the CONSORT checklist for reporting abstracts of RCTs had an effect on reporting quality found that results were better reported in journals which had an active editorial policy to implement the checklist.^25^

A scoping review conducted in 2017 by Blanco and colleagues summarised different interventions aimed at improving adherence to reporting guidelines.^26^ They identified a number of different interventions, some of which had been evaluated at journals. However, all the interventions, except requesting submission of checklists from authors, required additional resources from the journal (eg, internal peer review by editorial assistants or an additional peer-reviewer round conducted by a senior statistician using appropriate reporting guidelines.^27–29^ Therefore, it is unlikely that these interventions will be implemented in the majority of journals, especially smaller journals with limited resources. Another study found that providing authors with a web-based CONSORT tool, which combined different CONSORT extensions and provided authors with a customised checklist, did not improve reporting when used at the manuscript revision stage.^30^ However, a study examining ‘the nature and extent of changes made to manuscripts after peer review, in relation to the reporting of methodological aspects of RCTs’ and ‘the type of changes requested by peer reviewers’ found that peer review did lead to some improvement in reporting.^27^

The role of peer reviewers and expectations of them is varied.^31^ While CONSORT checklists are sometimes available for peer reviewers to check, they are not typically instructed to assess this information as part of their review and there have been no studies evaluating the effect of asking them to do this. We plan to evaluate the impact of giving peer reviewers a short version of the CONSORT checklist together with a brief explanation of the items and asking them to check if they are adequately reported.

## Methods and analysis

### Objective

The objective of this study is to evaluate the impact of giving peer reviewers, during the standard peer review process, a short version of the CONSORT checklist (C-short) together with a brief explanation of the items and asking them to check if they are adequately reported in the manuscript.

### Study design

This study is a multicentre superiority RCT with submitted manuscripts as the unit of randomisation (figure 1; allocation ratio 1:1). This study protocol was written in adherence to the SPIRIT guidelines (online supplementary file).^32^

10.1136/bmjopen-2019-035114.supp2Supplementary data

**Figure 1 F1:**
[figure not shown]
Study flow chart. CONSORT, CONsolidated Standards of Reporting Trials; SPIRIT: Standard Protocol Items: Recommendations for Interventional Trials.

### Study setting and eligibility criteria

The population will be defined on two levels: included journals and included manuscripts.

#### Inclusion criteria for journals

Included journals must: (i) endorse the CONSORT statement by mentioning it in the journals’ Instruction to Authors; (ii) have published primary results of at least five RCTs in 2017 (identified using a PubMed search). To be efficient, we plan to contact (via email) the editors of eligible journals from specific publishers (eg, BMJ Publishing Group; Public Library of Science (PLOS)) instead of separate journals. A description of the requirements for participation and a short summary information sheet will be included as part of the email invitation sent to journal editors. If a journal is eligible, and the editor agrees to take part, the editor will need to provide access to their editorial system (eg, ScholarOne, Editorial Manager) to enable the external researcher (BS) to screen and randomise eligible manuscripts. In cases where this is not possible, we will explore with individual journals if it would be possible to grant limited access (eg, only rights to screen studies) or to handle the different steps without access to the editorial system (eg, screening through automated reports; intervention provided by a journal staff member) and that the emails for the intervention would be sent by a member of the editorial team.

#### Inclusion criteria for manuscripts

All new manuscript submissions reporting the primary results of RCTs, which the journal editor has decided to send out for external peer review. Since the 10 chosen CONSORT checklist items (C-short) are applicable to different study designs, we will include all manuscripts reporting the primary results of RCTs regardless of study design (eg, parallel group trial, cluster trial, superiority trial, non-inferiority/equivalence trials).

#### Exclusion criteria for manuscripts

Manuscripts clearly presenting secondary trial results, additional time points, economic analyses or any other analyses.Manuscripts which are clearly labelled as a pilot or feasibility study or animal studies.Manuscripts not sent for peer review.

Details of journal manuscript submission and peer review processes, including consent and potential confidentiality issues, will be discussed in detail with each journal by teleconference and/or face to face prior to the journal agreeing to take part to ensure that randomisation of manuscripts is feasible.

In participating journals, the external researcher (BS) will check at least twice a week (by screening automated submission lists) all research manuscripts that are sent out for external peer review. As soon as the first invited peer reviewer accepts the invitation to review, the manuscript will be randomised to the intervention or control arm (see ‘Randomisation’ for more details). It is possible that this process might be slightly different among various included journals (eg, that team members of a journal might be involved in the screening if limited or no access to the journal’s editorial system is granted).

### Interventions

#### Control group: usual practice

After accepting to review a manuscript, peer reviewers will receive the automated, journal specific standard email with general information as per each journal’s usual practice (eg, where to access the manuscript, date the peer review report is due).

#### Intervention group: C-short plus usual practice

After accepting to review a manuscript, peer reviewers will receive the automated, journal specific standard email with general information (identical to control group). In addition, peer reviewers will receive an additional email from the editorial office that includes a short version of the CONSORT checklist (C-short) together with a brief explanation of the items either as a table within the email or as an attachment based on the preferences and possibilities of the journal (table 1, online supplementary appendix 1). Peer reviewers will be asked to check whether the items in the C-short checklist are addressed in the manuscript and to request authors to include these items if they are not adequately reported. This second email (see online supplementary appendix 1), containing the C-short checklist together with a brief explanation, is not generated automatically within the existing journal editorial systems (eg, ScholarOne or Editorial Manager); it will be sent manually by a researcher (BS) from the journal’s editorial system or by a member of the journal’s staff. In both cases the email will appear to have come from the editorial office (not the researcher).

10.1136/bmjopen-2019-035114.supp1Supplementary data

**Table 1 T1:** The 10 most important and poorly reported consort items as defined by a group of experts on the CONSORT statement.^30^for better understanding key features were summarised within a short explanation (extracted from the CONSORT explanation and elaboration paper^11^ as well as from the COBWEB tool)^33^

Item	Section	CONSORT item	Short explanation
1	Outcomes (6a)	Completely defined pre-specified primary outcome measure, including how and when it was assessed	Is it clear (i) what the primary outcome is (usually the one used in the sample size calculation), (ii) how it was measured (if relevant; eg, which score used), (iii) at what time point and (iv) what the analysis metric was (eg, change from baseline, final value)?
2	Sample size (7a)	How sample size was determined	Is there a clear description of how the sample size was determined, including (i) the estimated outcomes in each group, (ii) the α (type I) error level, (iii) the statistical power (or the β (type II) error level) and (iv) for continuous outcomes, the SD of the measurements?
3	Sequence generation (8a)	Method used to generate random allocation sequence	Does the description make it clear if the ‘assigned intervention is determined by a chance process and cannot be predicted’?
4	Allocation concealment (9)	Mechanism used to implement random allocation sequence (such as sequentially numbered containers), describing any steps taken to conceal the sequence until interventions were assigned	Is it clear how the care provider enrolling participants was made ignorant of the next assignment in the sequence (different from blinding)? Possible methods can rely on centralised or ‘third-party’ assignment (ie, use of a central telephone randomisation system, automated assignment system, sealed containers).
5	Blinding (11a)	If done, who was blinded after assignment to interventions (eg, participants, care providers, those assessing outcomes)	Is it clear if (i) healthcare providers, (ii) patients and (iii) outcome assessors are blinded to the intervention? General terms such as ‘double-blind’ without further specifications should be avoided.
6	Outcomes and estimation (17a/b)	For the primary outcome, results for each group, and the estimated effect size and its precision (such as 95% CI)	Is the estimated effect size and its precision (such as SD or 95% CI) for each treatment arm reported? When the primary outcome is binary, both the relative effect (risk ratio, relative risk or OR) and the absolute effect (risk difference) should be reported with CI.
7	Harms (19)	All-important harms or unintended effects in each group	Is the number of affected persons in each group, the severity grade (if relevant) and the absolute risk (eg, frequency of incidence) reported? Are the number of serious, life threatening events and deaths reported? If no adverse event occurred this should be clearly stated.
8	Registration (23)	Registration number and name of trial registry	Is the registry and the registration number reported? If the trial was not registered, it should be explained why.
9	Protocol (24)	Where trial protocol can be accessed	Is it stated where the trial protocol can be assessed (eg, published, supplementary file, repository, directly from author, confidential and therefore not available)?
10	Funding (25)	Sources of funding and other support (such as supply of drugs) and role of funders	Are (i) the funding sources, and (ii) the role of the funder(s) described?

COBWEB, Consort-based WEB tool; CONSORT, CONsolidated Standards of Reporting Trials.

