#### Assessment of outcomes

The outcomes will be assessed independently by two (blinded or at least partially blinded; see ‘blinding’) outcome assessors with expertise in the design and reporting of clinical trials. Any disagreement will be resolved by consensus or if necessary by consulting a third assessor. To ensure consistency between reviewers, we will first pilot the data extraction form; any disparities in the interpretation will be discussed and the data extraction form will be modified accordingly.

Adequate reporting of items will be assessed in duplicate from published full-text publications following the same instructions as provided by the CONSORT C-short checklist.^11^ The following checklist items have, due to their complexity, sub-items which will be extracted separately. The sub-items are highlighted in the short explanation of the intervention (see table 1 and online supplementary appendix 1):

Outcomes (item 6a): (i) define primary outcome, (ii) how it was measured, (iii) at what time point and (iv) the analysis metric (eg, change from baseline, final value).Sample size (item 7a): (i) the estimated outcomes in each group, (ii) the α (type I) error level, (iii) the statistical power (or the β (type II) error level), (iv) for continuous outcomes, the SD of the measurements.Blinding (item 11a): Is the blinding status clear for the following persons: (i) healthcare provider, (ii) patients and (iii) outcome assessors.Funding (item 25): (i) the funding source, and (ii) the role of funder in the design, conduct, analysis and reporting.

All items will be judged as either ‘yes’ meaning adequately reported, ‘no’ meaning not adequately reported or not reported at all, or ‘NA’ meaning that this sub-item is not applicable for this RCT. Items with different sub-items will only be judged as adequately reported if all relevant sub-items were adequately reported.

The outcomes ‘time from assigning an editor to the first decision’, ‘proportion of manuscripts rejected after the first round of peer-review’ and ‘proportion of manuscripts that will be published in the journal under study’ will be extracted directly from the journal’s editorial system or provided by the journal.

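### Table 1's explanation of item 6 treats per-arm values with an SD as an effect size with its precision, so for non-binary primary outcomes an article without a between-group estimate can be scored adequate

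*Protocol article*

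**What the plan says.** Protocol article, Table 1, item 6 (Outcomes and estimation, 17a/b) has two wordings in one row. The CONSORT column reads "For the primary outcome, results for each group, and the estimated effect size and its precision (such as 95% CI". The short explanation opens with "Is the estimated effect size and its precision (such as SD or 95% CI) for each treatment arm reported" and then adds, for binary primary outcomes only, that "both the relative effect (risk ratio, relative risk or OR) and the absolute effect (risk difference) should be reported with CI".

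The section on the intervention group says the reviewers' additional email "includes a short version of the CONSORT checklist (C-short) together with a brief explanation of the items", so reviewers see both wordings.

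Under Assessment of outcomes, adequacy is judged from the published article "following the same instructions as provided by the CONSORT C-short checklist". That section lists sub-items for 6a, 7a, 11a and 25 and states that "Items with different sub-items will only be judged as adequately reported if all relevant sub-items were adequately reported". Item 17a/b is not on the list. The extraction form is piloted first, and "any disparities in the interpretation will be discussed and the data extraction form will be modified accordingly".

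**The concern.** The CONSORT item has two components: what happened in each group, and how large the difference between groups is, with its precision. The explanation folds them into one question about each arm. That is wrong in two ways. A single arm has no effect size in the sense of the item, and an SD measures variation between participants, not uncertainty about an effect.

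This would matter little if the table only guided reviewers. It is also the scoring rule for the primary outcome, where item 6 is one tenth of each article's score, and for the secondary outcome that considers each item separately. If articles with only mean (SD) per arm score 'yes', an article that gains an effect estimate and CI through peer review scores the same as one that does not. The item then cannot register the improvement it is meant to detect.

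**Working it through.** **1. The two wordings applied to typical articles**

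| Article reports, for its primary outcome | CONSORT column | Short explanation |
|---|---|---|
| Continuous: mean (SD) per arm and a p-value, no difference or CI | Not met (no effect estimate) | Can be answered yes: a value with an SD is given for each arm |
| Other non-binary: per-arm summary with a per-arm CI, no contrast | Not met | Can be answered yes |
| Binary: events and percentages per arm only | Not met | Not met: the second sentence requires relative and absolute effects with CI |
| Any type: group results and all required between-group effects with CI | Met | Met |

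The wordings disagree in the first two rows only, so the gap is confined to non-binary primary outcomes.

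**2. Does another rule close the gap?** The requirement that all parts be adequate is tied to items with sub-items, and 17a/b has none listed. Nothing there makes the assessor record the between-group estimate separately. The CONSORT wording in the same row would close the gap if assessors gave it priority, but the text does not say which wording governs.

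**3. The plan's own figures**

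- Table 3, scenario 1: (79+85+78+57+36+45+73+71+20+35)/1030 = 579/1030 = 56.2%, stated as 56%.
- Table 3, scenario 2: the first seven items sum to 453/103 = 4.398. Adding 3 × 0.90 = 2.70 gives 7.098, and 7.098/10 = 71.0%, stated as 71%.
- Scenario 1 sample size (difference 0.14, SD 0.25, 90% power, two-sided 5% t-test): 67.99, so 68 per arm, as stated.
- Scenario 2 sample size (difference 0.11, SD 0.25, 80% power): 82.05, so 83 per arm, as stated. Power at 83 per arm is 80.5%.

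**4. How far lax scoring could raise an arm mean.** The control rate for item 6 is 45/103 = 44%, so 56% of articles are not adequate. The share of these that would pass on per-arm values is not in the documents, so the whole range is shown (assumption). Mean = 71.0% + (rise in item 6)/10.

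| Share of failing articles passed | Item 6 | Ten-item control mean |
|---|---|---|
| 0% | 44% | 71.0% |
| 25% | 58% | 72.4% |
| 50% | 72% | 73.8% |
| 75% | 86% | 75.2% |
| 100% | 100% | 76.6% |

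The limit is 5.6 points. It would need every failing article to have a non-binary primary outcome and to pass. An equal rise in both arms leaves the difference between arms unchanged.

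**5. How much of the target effect item 6 carries (scenario 2)**

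- Scenario 2's 15% relative gain applied to item 6: 0.44 × 0.15 × 0.10 = 0.0066, or 0.66 points.
- The same absolute gain on all ten items: 0.11 × 0.10 = 0.011, or 1.1 points.

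If lax scoring removed that share entirely, the remaining difference and t-test power at 83 per arm would be:

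- 0.11 − 0.0066 = 0.1034: power about 75%.
- 0.11 − 0.011 = 0.099: power about 72%.

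Both ways of spreading the gain are illustrations. The three items set at 90% cannot take a full share of either (0.90 × 1.15 = 1.035; 0.90 + 0.11 = 1.01), so item 6 could carry somewhat more.

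**The case against.** The strongest case on the other side is that this is one loose phrase. The correct CONSORT wording is in the same row and assessors see it. They have expertise in trial reporting, they work in duplicate with a third assessor available, and the form is piloted and revised where readings differ. An item without sub-items is still judged as a whole, so leaving 17a/b unsplit does not make its parts optional. The extraction form is not shown and may already resolve the point.

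Most of this stands as a limit. The lax reading is permitted, not prescribed, and a sensible pilot might remove it. But piloting resolves only disagreements that surface: two assessors who both follow the explanation will agree with each other. The wording is also a stated scoring rule, not a detail left to another document.

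A reader might infer more than the text supports:

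- *That an article without a CI can pass whatever its outcome type.* The sentence on binary outcomes rules this out for them.
- *That the trial is biased.* The same rule applies in both arms, and nothing in the documents shows differential scoring.
- *That the 44% baseline is invalid.* It comes from an earlier study, and this team added the explanations. The article does not say how the earlier study scored the item, so the question stays open.
- *That the funding item has the same fault*, because assessors score "the role of funder in the design, conduct, analysis and reporting" while Table 1 asks only whether the funder's role is described. The longer phrase can be read as spelling out the shorter one, so it is not a demonstrated contradiction.

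**Conclusion.** The point holds for continuous and other non-binary primary outcomes. Table 1 gives item 6 two criteria that lead to different scores for the same article, and the scoring section does not choose between them. What is lost is validity and sensitivity on one tenth of the primary outcome and on the matching item-level secondary outcome.

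The size is modest. Item 6 accounts for about 0.66 points of scenario 2's 11-point target under a 15% relative gain, or about 1.1 points if the gain is equal across items. Losing that share completely would take power from 80.5% to about 75% or 72%. That would need nearly all failing articles to pass under the lax reading, and the documents give no figure for how many would. Nothing here makes the stated sample sizes or power wrong. The case for acting is that the correction is specific and cheap and that scenario 2 is planned at 80% power with little to spare.

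**What to change.** In the extraction form and under Assessment of outcomes, add 17a/b to the items with sub-items, all required:

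1. the primary-outcome result for each group;
2. a between-group effect estimate with its 95% CI or SE, for every outcome type, keeping the existing requirement of relative and absolute effects with CI for binary outcomes.

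State that a per-arm SD alone does not satisfy part 2. Any articles already extracted should be re-scored on this item.

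This matches the CONSORT wording reviewers already receive, so neither the reviewers' email nor the sample size has to change. The cost is a few lines in the form and, where extraction has begun, one item to re-score from published articles. There are two downsides. Adherence on item 6 will look lower. Reviewers who followed only the loose explanation will also have been guided to a laxer standard than the one scored, which the trial report should acknowledge.
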